#### Methods in analysis to handle protocol non-adherence and any statistical methods to handle missing data {20c}

In general, per-protocol analysis will be intended. To address the fact that complete protocol adherence is not always feasible in everyday clinical practice, all relevant cases will be included in the calculations as part of an intention-to-treat analysis.

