### Objectives {7}

In the current study, we aim to address the following hypotheses:

Primary hypothesis:Delirium incidence is lower in the intervention group than in the control group

Secondary hypotheses:2)Pain intensity is lower in the intervention group than in the control group3)Intraoperative: NOL values are lower in the intervention group than in the control group4)Postoperative: NRS values are lower in the intervention group than in the control.5)Pain medication consumption p.p. is lower in the intervention group than in the control group6)Postoperative nausea and vomiting (PONV) incidence is lower in the intervention group than in the control group

Exploratory analyzation:7)The above-mentioned effects differ depending on whether the subjects hear a speaker’s voice according to their own gender or not

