### Criteria for discontinuing or modifying allocated interventions {11b}

Consent to participate in the study can be withdrawn at any time, without giving reasons or obtaining any disadvantages for further medical care. In case of withdrawal from the study, personal data already obtained will be destroyed. Patients for whom there will be a short-term change in the anaesthetic procedure, e.g., to anaesthesia with sevoflurane, will be considered separately due to the increased risk of PONV.

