ALLOCATION														
Randomized allocation		●												
SAMPLES														
Blood sample			●											
Saliva sample			●											●
INTERVENTION														
Controll group				●										
SGS intervention group				●										
DGS intervention group				●										
OUTCOME VARIABLES														
4AT Delirium			●		●	●	●	●	●	●	●	●	●	
3DCAM Delirium								●	●	●	●	●	●	
Pain score (NAS)			●		●	●	●	●	●	●	●	●	●	●
Pain medication consumption			●					●	●	●	●	●	●	●
Comfort scale (NCS)			●		●	●	●	●	●	●	●	●	●	●
PONV wengritzky								●	●	●	●	●	●	
Sedline				●										
NOL				●										

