#### Plans to promote participant retention and complete follow-up {18b}

To enhance participant retention, trained junior investigators will supervise participants during their clinical stay. Study results as well as personal blood work results will be provided to patients at the study’s conclusion if they have agreed to receive them.

A 3-month follow-up will yield additional information on participants’ well-being, and, when needed, further supportive discussions will be arranged.

If participants choose to withdraw from the study, all data collected from them will be eliminated and excluded from the analysis. Withdrawal will be permitted at any point.

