### Statistical methods

#### Statistical methods for primary and secondary outcomes {20a}

To ensure normal distribution, the Kolmogorov–Smirnov test will be conducted prior to further analyses. Statistical significance will be considered at a *p*-value < 0.05. The primary outcome (postoperative delirium incidence) and other binary outcomes (e.g., incidence of postoperative nausea and vomiting, PONV) will first be compared between the intervention and control groups using the chi^2^ test. Continuous non-parametric variables will be analyzed with Mann–Whitney *U* tests, and parametric variables with Student’s *t*-test. To account for potential confounding effects of intraoperative and postoperative medication use, detailed data on the type and dosage of analgesics and sedatives will be collected. These variables will be included as covariates in multivariable logistic regression models for binary outcomes (e.g., delirium, PONV) and multivariable linear regression models for continuous outcomes (e.g., postoperative pain scores, NRS; intraoperative NOL index values). Confounders will be selected a priori based on clinical relevance and evidence from previous literature to avoid data-driven overfitting.

Medication-related parameters (e.g., total opioid dose, intraoperative sedative use) will also be analysed descriptively and compared between groups. Sensitivity analyses will be performed to assess the robustness of the results with and without adjustment for these covariates.

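### Per-protocol is named as the general analysis of a superiority trial, and the plan does not say whether it or intention-to-treat decides the primary hypothesis

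*Protocol article*

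**What the plan says.** All references are to the protocol article.

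- **Analysis sets, {20c}.** The first sentence is "In general, per-protocol analysis will be intended". The second observes that full adherence is not always achievable in routine care and concludes that "all relevant cases will be included in the calculations as part of an intention-to-treat analysis". Neither set is defined, and neither is called primary.
- **Primary hypothesis, Objectives {7}.** "Delirium incidence is lower in the intervention group than in the control group": a directional superiority hypothesis.
- **Primary test, {20a}.** Delirium and other binary outcomes "will first be compared between the intervention and control groups using the chi^2^ test". No population is attached to the test.
- **Timing of allocation, Table 1 in {13}.** The row "Randomized allocation" is marked in the baseline column (V0), which stands under the time before surgery. By {11a} the audio starts only after intubation.
- **Change of anaesthetic, {11b}.** "Patients for whom there will be a short-term change in the anaesthetic procedure, e.g., to anaesthesia with sevoflurane, will be considered separately", the reason given being the higher risk of postoperative nausea and vomiting (PONV).
- **Withdrawal, {11b} and {18b}.** Personal data already obtained are destroyed; "all data collected from them will be eliminated and excluded from the analysis".

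**The concern.** In a superiority trial, the comparison that randomisation protects is the one between all allocated patients in their allocated arms. A per-protocol set is chosen by what happens after allocation. In this trial those events (a change of anaesthetic, interrupted audio, withdrawal) may be related to a difficult operation or a long anaesthetic, and so to delirium risk. Putting per-protocol first reverses the usual order for this type of hypothesis.

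The second sentence of {20c} does not repair this. Intention-to-treat means every randomised patient, so a qualifier that admits only some cases contradicts the term. With two candidate analyses, no stated order and an undefined qualifier, two things remain open: which patients answer the primary question, and which of two results is reported as the answer once the allocation is known.

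**Working it through.** **1. The passages side by side.**

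| Question | Where an answer would stand | What is there |
|---|---|---|
| Which set decides the primary test? | {20a}, {20c} | {20a}: none named. {20c}: per-protocol in general, then intention-to-treat |
| Who is in the intention-to-treat set? | {20c} | Cases judged relevant; no definition |
| Who is in the per-protocol set? | {20c} | No definition |
| Are switched patients in the delirium analysis? | {11b} | Handled separately because of PONV; delirium not mentioned |
| Are withdrawn patients in any analysis? | {11b}, {18b} | No; their data are deleted |

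No other section settles the first question.

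**2. Which events fall after randomisation.** Allocation is at V0, surgery at V2. A change of anaesthetic or incomplete playback can occur between V0 and the end of V2, and withdrawal at any time. All can therefore occur after allocation. Intravenous anaesthesia is an inclusion criterion in {10}, so a switched patient is an obvious candidate for removal from a per-protocol set.

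**3. How few patients can matter (hypothetical counts).** From {14}: 248 × 1.10 = 272.8, taken as 273 and rounded up to 280, which is 140 per arm at 1:1. The control rate is the assumed 25%, so 35/140. The intervention counts are invented for illustration. The uncorrected statistic is

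χ² = (p₁ − p₂)² / [p̄(1 − p̄)(1/n₁ + 1/n₂)], with p̄ the pooled rate.

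- All patients: 35/140 vs 24/140, p̄ = 59/280 = 0.2107. χ² = 0.0786² / [0.2107 × 0.7893 × 2/140] = 2.60, p = 0.107.
- Three delirious patients removed from the intervention arm only: 35/140 vs 21/137, p̄ = 56/277 = 0.2022. χ² = 0.0967² / [0.2022 × 0.7978 × (1/140 + 1/137)] = 4.01, p = 0.045. With continuity correction p = 0.064.
- Three removed from each arm: 32/137 vs 21/137. χ² = 2.83, p = 0.092.

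The crossing of 0.05 therefore needs exclusions in one arm only and the uncorrected test.

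**4. Bias under stated assumptions.** Suppose there is no true effect (25% in both arms, 140 per arm). A fraction e of the intervention arm only is excluded, and those excluded have delirium risk q. The rate among those kept is r = (0.25 − e·q)/(1 − e), and the spurious difference is 0.25 − r. The last column is the two-sided rejection rate at nominal 5%, by normal approximation.

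| e | q | r | Spurious difference | Error rate |
|---|---|---|---|---|
| 5% | 35% | 24.5% | 0.5 points | 5.1% |
| 10% | 35% | 23.9% | 1.1 points | 5.5% |
| 10% | 50% | 22.2% | 2.8 points | 8.2% |
| 15% | 50% | 20.6% | 4.4 points | 13.2% |

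The values of e and q are assumptions; the article gives neither. If exclusions are equal in both arms and unrelated to risk, there is no bias.

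**5. What as-randomised analysis costs.** Suppose 10% of the intervention arm carries the control risk. The intervention rate becomes 0.9 × 12.5% + 0.1 × 25% = 13.75%. With 140 per arm against 25%, power is 66.5% two-sided (77.2% one-sided). A per-protocol set of 126 per arm at 12.5% has 72.2% (81.8%). The article does not state sidedness, so both are shown. Power does not argue for the as-randomised analysis; protection from selection does.

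**The case against.** The best defence is that {20c} does name intention-to-treat, and names it because imperfect adherence is expected. On a generous reading, per-protocol expresses a hope for adherence and intention-to-treat is what will be done. A journal article also condenses, and an analysis plan may define the sets. What stands of this is that intention-to-treat is not absent. The defence does not remove the point: the article commits itself to per-protocol first and then qualifies that in conflicting terms. A later plan could follow either sentence and claim consistency with the protocol.

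Three stronger readings are tempting, and the documents do not support them.

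- *A reader might infer that switched patients are excluded from the delirium analysis.* {11b} does not say so. Separate handling may mean a subgroup or separate reporting, and the stated reason, "will be considered separately due to the increased risk of PONV", concerns a secondary outcome. The fault is that the section leaves the matter open.
- *A reader might infer that exclusions will differ by arm.* Patients, clinical staff and data collectors are blinded ({17a}), players are numbered and staff may not listen to them ({16b}), and controls receive two silent tracks ({11a}). Switches and interrupted playback should arise similarly in both arms. Blinding makes arm-dependent exclusion less likely. It does not prevent a choice between analyses after unblinding, and it cannot rule out exclusions caused by an effect of the intervention.
- *A reader might infer that per-protocol analysis leaves the trial short of power.* Removing 10% of 280 leaves 252, still above the 248 that {14} asks for after drop-out, and step 5 of the working shows that the dilution runs the other way.

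**Conclusion.** The point holds as one of reversed or unclear priority. The article puts per-protocol first for a superiority hypothesis, adds an intention-to-treat analysis of an undefined set, and does not say which one decides. It also leaves open whether patients with a change of anaesthetic stay in the primary delirium comparison, and it deletes withdrawn patients' data without saying how that fits an intention-to-treat set.

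The defect in the text is certain, but the size of any resulting bias is unknown because no non-adherence rate is given. Under the assumed one-arm exclusions the two-sided error rate ranges from about 5% to 13%; with balanced, risk-neutral exclusions it stays at 5%. The p-value example shows only that three patients can move a result across 0.05 when they are taken from one arm and the uncorrected test is used. Because the question is which patients answer the primary hypothesis, it must be settled before unblinding.

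**What to change.** Before unblinding:

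1. **{20c}.** State that the primary analysis includes all randomised patients in their allocated arm, including those with a change of anaesthetic or incomplete audio. Delete *relevant*. Define any unavoidable departure (for example, no surgery performed, or data deleted on withdrawal), and count and report it by arm. Define the per-protocol set and call its analysis supportive only.
2. **{20a}.** Attach this population to the primary chi-square test.
3. **{11b}.** State that patients with a change of anaesthetic stay in the primary analysis, with a sensitivity analysis that leaves them out. This concerns analysis only, not their care.
4. **{11b} and {18b}.** Reconcile the deletion of withdrawn patients' data with the intention-to-treat set. If deletion stands, say that the set is incomplete for this reason and report the number withdrawn by arm.

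The cost is a few sentences of analysis wording and the by-arm reporting of departures. The target of 280 and the conduct of the trial do not change. The downside is some dilution of the effect by non-adherent patients, and hence somewhat lower power than a per-protocol analysis (66.5% against 72.2% two-sided under the assumptions in step 5 of the working).

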#### Plans to give access to the full protocol, participant level-data and statistical code {31c}

N/a.

### Oversight and monitoring

#### Composition of the coordinating center and trial steering committee {5d}

N/a.

#### Composition of the data monitoring committee, its role and reporting structure {21a}

The study design, inclusion criteria, questionnaire selection, the points at which questioning takes place, together with supplementary monitoring and data-gathering monitors and the documentation tool RedCap were primarily prepared, selected and refined by the main center. In consultation with the other centers, details were negotiated through an iterative process to ensure a unified basis for conducting the study. As the study is self-funded and there are no sponsors involved, there are no competing interests or conflicts of interest. Trained junior researchers of the LMU Munich [27] hospital will monitor the process of data collection and report regularly to their head of trial.

#### Adverse event reporting and harms {22}

Adverse events, such as an increase in pain intensity or increased consumption of antiemetics, as well as delayed awakening after prolonged general anesthesia, will be closely monitored continuously and treated immediately.

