### Participant timeline {13}

The study duration for all included participants will be defined by the time of surgery until the day of discharge. A follow-up survey of the cognitive function level is planned after 3 months (follow up). The postoperative follow-up point in time was determined by the fact that, at this juncture, patients have customarily concluded their postoperative inpatient rehabilitation and have resided in their domestic environment for a period of several weeks. This period represents the earliest time frame in which daily functioning can be meaningfully assessed, without the confounding influence of ongoing rehabilitation measures or acute postoperative recovery processes. Therefore, it enables a valid evaluation of cognitive performance and its effect on daily living activities under stable conditions. Moreover, the timing of the follow-up assessment is consistent with international recommendations for the evaluation of postoperative POCD and associated outcomes. Evered et al. propose that cognitive testing for POCD should be conducted a minimum of 3 months after surgery, with the aim of avoiding the capture of transient, early postoperative changes [8]. While the MoCA was administered at baseline as an inclusion criterion to confirm adequate cognitive status at 3-month follow-up, no cognitive screening tool was applied. Instead, the assessment focused on functional outcomes using the SF-36 and iADL, as these measures are more directly aligned with capturing everyday functioning. Given the nationwide recruitment, follow-up instruments were selected to allow remote completion and ensure high response rates. Table 1 shows a detailed overview of the course of the study.

**Table 1 Tab1:** Participant timeline

	STUDY PERIOD													
Date	Prior to surgery		Day of surgery						Day 1	Day 2	Day 3	Day 4	Day 5	+3 months
Timepoint	Screening	Baseline	Pre-OP	OP	PostOP recovery room				PostOP ward					Follow-Up
Visit-Code	SCR	V0	V1	V2	V3a	V3b	V3c	V3d	V4	V5	V6	V7	V8	V9
ENROLMENT														
Eligibility criteria	●													
Informed consent	●													
Feedback request	●													
ASSESSMENTS														
MOCA		●												
TMT		●												
Frailty Screening		●												
PONV risk-score		●												
Charlson Comorbidity Index		●												
Permanent medication		●												
QUESTIONNAIRES														
iADL		●												●
SF36		●												●
GDS		●												●
BDI														●
Complications														●

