##### After surgery

After extubating objective data will be collected in the recovery room every 15 min for a total duration of 1 h. Postoperative assessments will include the 4AT score for delirium, pain score measured on NRS, Numerical Comfort Scale (NCS) for assessing comfort, and postoperative nausea rated from 0 to 3. After the patient will have been in the recovery room for 1 h, additional assessments will be conducted, including an extended delirium screening (3DCAM), PONV Score antiemetic consumption, and nurse-controlled analgesia consumption for NRS 3.

In the regular ward, data will be recorded for the first 5 days post-surgery: pain scores (measured using the NRS); analgesic intake via nurse-controlled analgesia (NCA; applicable for NRS of 3 or higher); PONV scores (as per Wengritzky’s classification system); antiemetic usage, comfort ratings (using the NCS); and delirium assessments (using both the 4AT score and 3DCAM) will be documented.

Follow-up assessments will be conducted 3 months after the surgery by sending patients a set of questionnaires (iADL, GDS, BDI, SF36) via mail. They will also be asked to provide their pain and comfort levels (NAS and NCS, respectively) and to submit another saliva sample. Any adverse effects that may have occurred will also be investigated and noted. If any cause for concern arises about returned questionnaires, the participants will be contacted and offered further assistance. All study participants may contact us at any time should they have any questions or concerns.

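### Adverse events are said to be monitored continuously, but the only scheduled complications item is at the 3-month questionnaire visit, so recording of any complication beyond the three named events depends on the 3-month reply

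*Protocol article*

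**What the plan says.** The section on adverse event reporting and harms {22} names "Adverse events, such as an increase in pain intensity or increased consumption of antiemetics", and also delayed awakening, and states that these "will be closely monitored continuously and treated immediately".

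Table 1 (Participant timeline {13}) has one row for harms, "Complications". It stands in the questionnaire block and is marked only at V9, three months after surgery. No visit from V2 (operation) through V3a–V3d (recovery room) to V4–V8 (ward days 1 to 5) carries a complications or adverse-event item.

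The text under After surgery {18a} agrees with the table. Its recovery-room and ward lists cover delirium, pain, comfort, nausea or PONV, analgesics and antiemetics. Adverse effects are mentioned only in the follow-up paragraph. That paragraph says the 3-month assessment is done "by sending patients a set of questionnaires (iADL, GDS, BDI, SF36) via mail" and adds: "Any adverse effects that may have occurred will also be investigated and noted".

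**The concern.** The article makes two statements about when harms are recorded, and they differ. One says continuously. The other, a visit-by-visit schedule supported by the data-collection text, puts the only general complications item at three months.

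If the schedule is followed as written, a complication in hospital that is not one of the three named events has no recording point while study staff are seeing the patient. It enters the data only if the 3-month contact succeeds. A patient who has died cannot reply, and one who is ill or cognitively impaired is less likely to. The Background {6a} links postoperative delirium with greater morbidity, longer stay, long-term cognitive decline and higher mortality. Non-reply is therefore plausibly related to the primary outcome, and the complication data could be incomplete in a selective way.

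**Working it through.** **Step 1: which harms are captured in hospital**

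| Event | Where it is recorded | Depends on the 3-month reply? |
|---|---|---|
| More pain | Pain score every 15 min for 1 h, then days 1–5 (After surgery; Table 1, V3a–V8) | No |
| More antiemetic use | After the recovery-room hour and on the ward, days 1–5 (After surgery) | No |
| Delayed awakening | Time from end of sedation to extubation (Throughout surgery) | No |
| Any other complication | Table 1 at V9 only; adverse effects in the 3-month paragraph | Yes, as described |

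Delirium itself is also assessed in hospital (4AT at V3a–V8, 3D-CAM at V3d–V8). The gap is confined to the last row.

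**Step 2: is there a route for patients who do not reply?**

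The follow-up paragraph foresees contacting participants when a returned questionnaire gives cause for concern. It describes no contact with those who return nothing.

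**Step 3: how large could the loss be?**

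The article gives no return rate and no complication rate, so there is no stated figure to reproduce. Everything in this step is assumption, apart from the target of 280 patients (Sample size {14}).

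*Missing forms* = 280 × (1 − reply rate):
- 90% reply: 28 missing
- 80% reply: 56 missing
- 70% reply: 84 missing
- 60% reply: 112 missing

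*Observed risk* = p·r1 / (p·r1 + (1 − p)·r0). Here p is the true complication risk, and r1 and r0 are the reply rates with and without a complication. Take p = 10% and r0 = 90%:
- r1 = 90%: 0.090 / (0.090 + 0.810) = 10.0%
- r1 = 70%: 0.070 / (0.070 + 0.810) = 8.0%
- r1 = 50%: 0.050 / (0.050 + 0.810) = 5.8%

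If reply does not depend on having had a complication, the rate is unbiased and only events are lost. If it does, the rate is understated as well.

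*Two quantities to keep apart.* Assume complication rates of 8% in those who return the form and 20% in those who do not.
- 10% non-return: true rate 0.90 × 8 + 0.10 × 20 = 9.2%. The observed 8% understates the rate by 1 − 8/9.2 = 13%. The share of events never recorded is 2.0/9.2 = 22%.
- 25% non-return: true rate 0.75 × 8 + 0.25 × 20 = 11.0%. The rate is understated by 1 − 8/11 = 27%. The share of events never recorded is 5.0/11.0 = 45%.

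**The case against.** **Table 1 is a summary.** Antiemetic use, operating time, recovery duration and the 0–3 nausea rating are all collected according to the text, yet none has its own row. A missing mark does not prove that nothing is recorded, and adverse-event forms may be described in the full protocol, which is not shown. This stands as a caution, and the absence of such forms from an article is not the point here. The point is that the article does schedule a complications item, places it at one visit, and elsewhere states a different timing. The antiemetic and recovery-time items at least appear in the text for the in-hospital period; complications do not.

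**The named events are examples, and adverse effects are to be investigated.** The wording allows other events and suggests more than a self-report form. The mailed set is listed as iADL, GDS, BDI and SF-36, without a complications form. This also stands: that the item is mailed is inferred from its place in Table 1 and from the adjoining sentence. Either way, the recording is tied to the 3-month contact.

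**High response is expected.** The Participant timeline says the follow-up instruments were chosen with response rates in mind. No expected rate is given, so this does not settle the matter.

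**The named harms overlap with efficacy outcomes.** Two of the three are secondary outcomes in the unfavourable direction. For an audio track added to otherwise identical care, these are reasonable harms to name, and the overlap is no error.

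**Conclusion.** The concern holds in a limited form. The harms section and Table 1 state different timings and must be reconciled. As the article stands, recording of complications other than pain, antiemetic use and delayed awakening depends on the 3-month reply. That the reply is selective is plausible from the article's own account of delirium but is not shown. The size of the loss is unknown; the figures above only show what assumed reply patterns would do.

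A reader might infer that the trial's whole harm comparison rests on patients well enough to reply. The documents do not support that. The three named events are measured in hospital by study staff, and the article defines no between-arm harm comparison that could rest on the form.

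Nor does it follow that the intervention would look falsely harmless. Under the primary hypothesis delirium is more frequent in controls. If patients with delirium reply less, complications would be under-recorded more in the control arm, and the intervention would look worse. The primary outcome and its analysis are unaffected. This is a worthwhile, inexpensive improvement.

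**What to change.** Reconcile the harms section with Table 1:

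1. Mark complications at V2 to V8 as well as V9. Complete the item at the visits already made, using the patient file that the team already reviews for medication (Outcomes {12}).
2. Report complications by randomised arm, separately from the NRS and antiemetic outcomes.
3. Report the number of 3-month forms returned in each arm, so that the reader can judge the completeness of the V9 item.

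The cost is one short form in the existing REDCap database and a little data-entry time, with no new visit, assessor or procedure. Enrolment began in November 2022 (Trial status). For patients already treated, the item would have to be completed retrospectively from the hospital file, by staff who remain blinded and in the same way in all arms.

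A hospital-record check of vital status and readmission for those who do not reply at three months would close more of the gap. It is optional and would be new work, because the contact now foreseen covers only returned questionnaires. It would also miss readmissions to other hospitals.
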